**Table 1 Tab1:** **Characteristics of EMPOWER-PAR Intervention Clinics and Control Clinics**

Clinic characteristics		Geographical location	Workload (average number of patients seen in the clinic per day)	Staffing (number of doctors and allied health personnel)
Pair no. 1	**Intervention**	**Urban**	**900**	**30**
	Control	Urban	900	28
Pair no. 2	**Intervention**	**Urban**	**600**	**27**
	Control	Urban	650	29
Pair no. 3	**Intervention**	**Urban**	**550**	**32**
	Control	Urban	500	33
Pair no. 4	**Intervention**	**Sub-urban**	**500**	**22**
	Control	Sub-urban	500	20
Pair no. 5	**Intervention**	**Sub-urban**	**350**	**21**
	Control	Sub-urban	400	19

### Patient recruitment

This study recruited consecutive T2DM and/or HPT patients who attend the selected clinic within the 2-week recruitment period. These patients were given the patient information sheet in the waiting area. Informed consent forms were obtained from those willing to participate. Screening was conducted to identify eligible participants based on the inclusion and exclusion criteria. Eligible patients were then enrolled in the study.

#### Inclusion criteria

Males and females aged ≥ 18 years who were:diagnosed with T2DM and/or HPTseen at least once in the last year at the primary care clinic for the above condition(s)

#### Exclusion criteria

type 1 diabetes mellitusreceiving renal dialysispresenting with severe HPT (Systolic BP > 180 mmHg and/or Diastolic BP > 110 mmHg)diagnosed with conditions resulting in secondary hypertensiondiagnosed with circulatory disorders requiring referral to secondary care over the last year (e.g. unstable angina, heart attack, stroke, transient ischaemic attacks)receiving shared care between primary and secondary care for complications of T2DM and/or HPTpregnancyenrolled in another studyAll patients in the intervention arm were required to be seen at least twice by the CDM team of each clinic during the 1-year intervention period. Those who did not comply were considered as lost to follow-up. There was no limit to the number of clinic visits a patient was allowed to make in either arm during the course of the study. Figure 1 shows the EMPOWER-PAR Trial Profile outlining the enrolment of public primary care clinics and the recruitment of patients.

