#### Phase 3: Facilitation and support to implement the intervention

Each clinic was assigned two facilitators to coach the CDM team, facilitate and guide the implementation of intervention and provide feedback on their performance. Facilitators were the investigators, all of whom are qualified FMS or clinical epidemiologists. The facilitators conducted two follow-up site visits over the 1-year intervention period. The visits occur at 3 months and 9 months. During the visits, the facilitators met the CDM team to collect information on the implementation process, discuss the challenges and document the progress in the clinics. Similar data were also collected during the intervention review workshop at 6 months. This information was analysed, and detailed feedback were then provided to each clinic. It is believed that, through this collaborative process of coaching and feedback sessions, optimal implementations tailored to the needs of each clinic could be achieved.

The control clinics continued with usual care with no additional intervention. The CDM workshop modules and intervention tools will be made available to the control clinics at the end of the study. There were no other additional resources allocated to either the intervention or the control group.

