### Outcome measures

Outcome measures were obtained from both intervention and control clinics at baseline and one year after the commencement of the intervention.

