#### Sample calculation for T2DM patients

A sample size of 626 (313 in each arm) was obtained by sampling 10 clusters (5 intervention vs 5 control) with 63 subjects from each cluster to achieve 91% power to detect 25% difference in the proportion of subjects achieving target HbA1c < 6.5% from baseline and between the intervention and control groups. The test statistic used was the two-sided Z-test (unpooled). The significance level of the test is 0.05. Therefore, after allowing for 25% dropout rate, this study aimed to recruit a total sample of 836 T2DM patients at baseline (i.e. 418 in each arm and 84 from each clinic).

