#### Sample calculation for HPT patients without T2DM

A sample size of 438 (219 in each arm) was obtained by sampling 10 clusters (5 intervention vs 5 control) with 44 subjects from each cluster to achieve 88% power to detect 25% difference in the proportion of subjects achieving target BP < 140/90 mmHg from baseline and between the intervention and control groups. The test statistic used was the two-sided Z-test (unpooled). The significance level of the test is 0.05. Therefore, after allowing for 25% dropout rate, this study aimed to recruit a total sample of 584 HPT patients at baseline (i.e. 292 in each arm and 58 from each clinic).

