### Statistical analysis

The statistical analysis plan to test the primary hypotheses of the study is described. Continuous variables will be described by summary statistics (means and standard deviations) for normally distributed variables. If the distribution is not normal, median with inter-quartile range will be reported instead. Other descriptive statistics, such as minimum and maximum values will be reported when necessary. Categorical (nominal/ordinal) variables will be described by frequencies with percentages. All outcomes are treated as categorical variables (e.g. proportions of patients achieving targets for HbA1c and BP). To assess the differences in the proportions of patients who are able to reach the treatment goals by their intervention strategy, a generalized estimation equation model that adjusts for clustering effects will be used. The model will be an independent working model. Treatment effects will be obtained using the estimated marginal means and differences will be tested using the Wald chi-square tests. The power of the study will be recalculated based on the effect size and after taking into account the clustering effect of the study design. An intention-to-treat analysis will be conducted, and *P-values* of less than 0.05 will be considered significant. All analyses will be carried out using SPSS (IBM Corp. Released 2011 IBM SPSS Statistics for Windows, Version 20.0. Armonk, NY: IBM Corp.).

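### Loss to follow-up is defined by contact with the intervention team, in one arm only; this does not fit the stated intention-to-treat analysis and may bias both primary comparisons

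*Protocol article*

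**What the plan says.** The closing text under Exclusion criteria sets a minimum of two CDM-team contacts in the intervention year for patients in the intervention arm, and continues: "Those who did not comply were considered as lost to follow-up".

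The only visit statement there that covers both arms concerns an upper limit: "There was no limit to the number of clinic visits a patient was allowed to make in either arm". No minimum is given for controls. Phase 3 of the implementation section says of them: "The control clinics continued with usual care with no additional intervention".

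Outcome measures describes the same collection in both arms: "Outcome measures were obtained from both intervention and control clinics at baseline and one year after the commencement of the intervention".

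Statistical analysis says: "An intention-to-treat analysis will be conducted". It does not say how patients classed as lost are handled.

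**The concern.** Loss to follow-up ordinarily means that the outcome could not be obtained. Here it means that the patient received too little of the allocated intervention. A patient with one CDM-team contact and a valid 1-year HbA1c is lost if the clinic was allocated to the intervention. On the text available, a control patient who attended equally rarely is not. Under intention-to-treat, low exposure to the allocated treatment does not change a patient's follow-up status.

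Three features of this trial make the point matter:

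- Appointment systems, reminders and defaulter tracing are part of what the CDM teams are trained to set up (workshop 1 in Table 2). Too few contacts can therefore be a failure of the intervention itself, and the rule relabels that failure as loss.
- The Discussion expects staff turnover, workload and short consultations to hamper delivery. Patients whom a stretched clinic did not reach would be classed as lost.
- The Discussion wants to conclude that the intervention works in real life. An intervention arm restricted to patients who received enough of it could not support that claim.

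Both primary outcomes are proportions at target, so any arm-specific selection of patients enters both comparisons directly.

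**Working it through.** **1. The plan's own dropout figures.** Both sample size sections allow 25% dropout: "after allowing for 25% dropout rate, this study aimed to recruit a total sample of 836 T2DM patients at baseline" and "after allowing for 25% dropout rate, this study aimed to recruit a total sample of 584 HPT patients at baseline". Using N/(1 − 0.25):

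- T2DM: 313/0.75 = 417.3, so 418 per arm, as stated. The total 626/0.75 = 834.7 gives 835; the stated 836 is 2 × 418.
- Hypertension without T2DM: 219/0.75 = 292 per arm and 438/0.75 = 584 in total, as stated.

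The figures reproduce. This arithmetic treats dropouts as outside the analysed number, and the same 25% is applied to both arms. It is a routine allowance and does not define the analysis set.

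**2. Bias if the patients are left out.** Assume no true effect. Let p be the proportion at target among all patients, q the share of intervention patients failing the two-contact rule, p_A and p_N the proportions at target among those meeting and failing it, and d = p_A − p_N. Since p = (1 − q)·p_A + q·p_N, it follows that p_A − p = q × d.

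The document gives neither q nor d. As assumptions:

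- q = 5%, d = 5 points: +0.25 points
- q = 10%, d = 10 points: +1.0 point
- q = 15%, d = 15 points: +2.25 points
- q = 25%, d = 20 points: +5.0 points

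The last line is an extreme corner for T2DM. With the background rate of 18.1% quoted in the Background, it implies p_N = 18.1 − 0.75 × 20 = 3.1%. Also, 25% is the plan's allowance for dropout of any cause, not an estimate of failure of the two-contact rule.

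**3. Allowing for control losses.** If a share q_C of controls is also unmeasured, with gap d_C, the net bias is q·d − q_C·d_C. With d_C of zero or more, q × d is an upper bound. It is reached only when control losses are nil or unrelated to disease control, and equal losses on both sides cancel.

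**4. Bias if the patients are counted as failures.** The intervention proportion becomes (1 − q)·p_A, so the bias is (1 − q)·p_A − p = −q·p_N, which is zero or negative.

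**5. The two handlings side by side.** Take the Background rates (18.1% for HbA1c; 60.1% for blood pressure in hypertension without T2DM), q = 25%, and assume p_N is half of p_A. Then p_A = p/(0.75 + 0.125):

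- T2DM: p_A = 20.7%, p_N = 10.3%. Left out: +2.6 points. Counted as failures: −0.25 × 10.3 = −2.6 points.
- Hypertension: p_A = 68.7%, p_N = 34.3%. Left out: +8.6 points. Counted as failures: −0.25 × 34.3 = −8.6 points.

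The hypertension case implies d = 34.3 points, beyond the 20-point end of the range in step 2. It shows the change of sign and the dependence on the background rate; it is not a likely value.

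**6. Scale.** The trial is powered for a 25% difference. If that is read as absolute points, 0.25 to 5 points is 1% to 20% of it. The earlier non-randomised Malaysian private-clinic trial cited in the Background found 69.6 − 57.6 = 12 points for blood pressure at 6 months.

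**The case against.** The strongest reply is that nothing in the article says these patients are removed. They are classed as lost, and the only statement about the analysis set is intention-to-treat. A patient can be lost and still belong to that set, and the handling of missing outcomes is commonly left to an analysis plan, which is not shown. The dropout inflation is compatible with exclusion but does not establish it. All of this stands.

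The direction is also open. The rule counts contacts with the CDM team, not clinic attendance. Some patients may fall short because the clinic was short of staff. If teams gave priority to poorly controlled patients, those below two contacts could be the better controlled ones, and leaving them out would work against the intervention. Controls who rarely attend may be unmeasured too, since the outcomes need physical measurements and fasting blood. These points stand, and they make q × d an upper bound rather than an estimate. Figure 1, the trial profile, could not be read and might contain a control-arm rule.

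What does not stand is that the matter can simply be left to the analysis plan. The one-arm definition is stated text, not a missing detail. If the label has no effect on the analysis, it describes adherence and should be called that. If it has an effect, the analysis departs from intention-to-treat.

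**Conclusion.** The inconsistency holds: an exposure-based definition of loss, stated for the intervention arm only, sits beside an intention-to-treat analysis. It may bias both primary comparisons.

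A reader might infer more: that intervention patients with few contacts are dropped and the effect is therefore overstated. The document does not support that as a fact. It would need these patients to be excluded, to be less well controlled than the rest, and not to be matched by comparable control losses. If all three hold, the bias favours the intervention by at most q × d, about 0.25 to 5 points under the assumed ranges. If the patients are counted as failures, the bias is zero or against the intervention. If they are left out but do as well as the others, it is zero. Direction and size cannot be settled from the document.

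**What to change.** Reconcile the closing text of Exclusion criteria with Statistical analysis before the outcome comparison is run:

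- Define loss to follow-up identically in both arms as no 1-year outcome measurement.
- Analyse every enrolled patient in the arm to which the clinic was allocated, using any 1-year HbA1c or blood pressure obtained, whatever the number of CDM-team contacts.
- Handle missing outcomes by the same method in both arms.
- Report the two-contact criterion only as an adherence measure or in a labelled per-protocol sensitivity analysis.

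For patients whose 1-year outcome was measured, the cost is a change of wording and a re-flagging of records. Trial status says that outcome collection ran from January to June 2014 and that cleaning and analysis had just begun. The estimate may become less favourable to the intervention. If patients classed as lost were never measured, re-flagging cannot recover their outcomes; these should be reported as missing, by arm.

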**Figure 1 Fig1:**
[figure not shown]
**EMPOWER-PAR Trial Profile: Enrolment of Public Primary Care Clinics and Recruitment of Patients.**

### The EMPOWER-PAR intervention

The study intervention, referred to as the EMPOWER-PAR intervention, was developed in accordance with Medical Research Council guidance on developing and evaluating complex interventions to improve health outcomes [41] and was implemented at the primary care clinics for a period of one year. The underlying framework in developing the complex intervention for EMPOWER-PAR was based on six interrelated elements of the CCM [21–23]. The six elements are 1) organisation of health care (i.e. providing leadership and minimising barriers to care), 2) self-management support (i.e. facilitating skills-based learning and patient empowerment), 3) decision support (i.e. providing guidance for implementing evidence-based care), 4) delivery system design (i.e. coordinating care processes), 5) clinical information systems (i.e. tracking progress through reporting outcomes to patients and providers) and 6) community resources and policies (i.e. sustaining care by using community-based resources) [21–23].

Three obligatory components that define the EMPOWER-PAR intervention were developed based on four interrelated elements of the CCM (organisation of health care, delivery system design, self-management support and decision support). These intervention components utilise readily available and existing resources in the Malaysian public primary care setting:I.Creating/Strengthening a CDM team—a multidisciplinary team led by FMS to improve coordination of care for T2DM and/or HPT and co-existing CV risk factorsII.Utilising the Global CV Risks Self-Management Booklet to support patients self-managementIII.Utilising the Clinical Practice Guidelines (CPG) for T2DM [42] and HPT [43] to assist with management and prescribing

Two optional components of the EMPOWER-PAR intervention were developed based on the other 2 CCM elements (clinical information system and community resources):I.Utilising clinical information system and conducting clinical audits to track progress through reporting outcomes to patients and providersII.Utilising community resources to support and sustain care

### Evidence on the chronic care model and participatory action research approach as the underpinning conceptual frameworks for the EMPOWER-PAR intervention

The CCM has been identified by global health policy experts as the most advanced in terms of conceptualisation and design, and in the range of evidence supporting it [16, 34]. Several systematic reviews [26–28, 44] and a meta-analysis [45] evaluating the impacts of the CCM have demonstrated the effectiveness of this model in a variety of settings, pathologies and target groups. Evidence has also shown that system approaches addressing even one of the components have been helpful in improving quality [27]. Some researchers have even attempted to identify which of the individual CCM elements were the most effective, despite the difficulty of disentangling the multifaceted elements. Organisation of health care that involves providing leadership and removing barriers to care is one the most important elements of the CCM [46–48]. Evidence has shown that measurable improvement in the care of patients with chronic conditions will only occur if system leaders make it a priority and provide the leadership, incentives and resources necessary to make improvements happen [46]. Delivery system design and self-management support have also emerged as powerful interventions [47, 48]. Decision support that integrates locally relevant evidence-based CPG into the fabric of patient care is fundamental to putting evidence into practice in managing chronic diseases [49].

In view of this evidence, the three obligatory components of the EMPOWER-PAR intervention were designed based on four interrelated CCM elements, namely organisation of health care, delivery system design, self-management support and decision support. These elements were chosen because of their individual strength in improving chronic care quality. In EMPOWER-PAR, the organisation of health care and delivery system design was delivered in the form of creating or strengthening the multidisciplinary CDM team and improving the coordination of care. The FMS had to be willing to lead the CDM team as well as the implementation of the intervention to be included in the study. Being the most clinically qualified member of the team, the FMS was ideally suited to take up the leadership role. The CDM team consists of multidisciplinary allied health personnel, and their roles are pivotal in improving the clinical outcomes, given the complexity of managing chronic conditions [50]. Evidence has shown that multidisciplinary interventions have resulted in significant improvement in glycaemic and BP control [51–53]. Delivery system design also involves training the CDM team to improve the coordination of care, particularly in the skills to develop and maintain clinic-based registries, an appointment system, reminder mechanisms and defaulter tracing. This element is central in improving the process of care for patients with chronic diseases whom require long-term follow-up, regular monitoring and promotion of adherence to treatment [50].

Self-management support was delivered to patients using the Global CV Risks Self-Management Booklet. The CDM team were trained in patient-centred communication and counselling skills to empower the patients to self-manage. There is ample evidence to show that application of these skills in delivering self-management support to patients improved glycaemic and BP control compared to usual care, beyond the benefits afforded by medications alone [54–56].

Decision support was delivered by training the CDM team to utilise the CPG on T2DM [42] and HPT [43] to improve management and prescribing. Evidence from other studies suggested that adherence to evidence-based prescribing guidelines for hypertension resulted in substantial savings in prescription costs [57]. Although the implementation of the other two CCM elements (clinical information system and community resources) as part of the EMPOWER-PAR intervention was optional, evidence supporting their role in CDM is also robust [58, 59].

Despite strong evidence supporting the individual elements of the CCM, there is a paucity of literature regarding implementation of the entire CCM as a multifaceted intervention, especially in developing countries. With the exception of the CORFIS study [35], previous studies implementing the entire CCM as multifaceted intervention have been conducted in developed countries [60, 61]. Similar to CORFIS, the EMPOWER-PAR is not designed to differentiate the effectiveness of individual CCM elements in its multifaceted intervention.

Successful CCM implementations have also been shown to work best within the pragmatic environment using a collaborative approach and coaching initiatives aiming at empowering health care providers to improve clinical practice [24]. External guidance and the participation of multidisciplinary health care team members during the process have been shown to be the contributing factors towards successful implementation and real transformation [24]. However, contextual factors within different clinic settings may influence the ability of teams to make and sustain changes in care. Although the selected clinics have great similarities, the existing system of care for chronic diseases may differ substantially. Each clinic may already have a pre-existing chronic disease management system, and these are at different stages of development depending on the experience of the FMS in charge and their duration of service at the clinic. Clinics with an experienced and longer serving FMS may be more advanced in their system development for chronic disease care. Furthermore, there may be local challenges resulting in the different stages of the development. The challenges include shortages or high turnover of medical staff and allied health personnel, limited clinic space, high patient load and time constraints. These differences demand different levels of intervention and expertise for improvement, and imposing a rigid intervention program is impractical and inappropriate. Hence, this study did not impose a strict protocol, and some flexibility on how the intervention program was implemented was allowed in line with the needs and constraints of the clinics.

The PAR approach [25, 40] was therefore adopted in designing and implementing the EMPOWER-PAR intervention. This process requires active participation of the CDM team from each clinic to design, propose and implement the intervention program based on the four CCM elements that define the intervention. In PAR, the researchers attempt to democratise the research process [25]. The iteration of reflection and self-analysis of the intervention, together with the power sharing in the research process are the main characteristics of PAR [25, 40]. Participants who were passive players in the beginning would eventually become active players [25]. The PAR component ensured that the primary care providers involved in this study were empowered to make the choice of actions within their constraints to improve their patients’ health outcomes. The process of PAR allows the primary care providers to have increased autonomy to determine how best to improve the quality of their patient care [25].

